## Abstract

Pediatric sleep-disordered breathing (SDB) is underdiagnosed despite its associations with adverse neurobehavioral, psychosocial, and cardiometabolic outcomes. Pediatric dental providers routinely evaluate craniofacial growth and maintain longitudinal contact with children, yet practical approaches for integrating SDB risk assessment into dental settings remain limited. This protocol describes a prospective, cross-sectional observational study that will enroll 60 school-aged children aged 8–13 years from a university-based pediatric dental clinic and classify them as low-risk or high-risk for SDB using the Pediatric Sleep Questionnaire (PSQ; threshold ≥ 0.33). The primary aim is to examine associations between PSQ-based risk classification and objective physiologic sleep parameters, including the Apnea–Hypopnea Index, Respiratory Disturbance Index, Sleep Apnea Indicator, and Sleep Quality Index, obtained from a U.S. Food and Drug Administration-cleared wearable home sleep monitor—SleepImage Ring (MyCardio LLC, Denver, CO, USA)—worn for a minimum of three consecutive nights. Secondary aims will evaluate associations between SDB risk classification and body mass index, Mallampati score, Brodsky tonsillar grade, and psychosocial functioning (anxiety, depression, perceived stress, and daytime sleepiness). Exploratory craniofacial analyses will be conducted among participants with clinically available lateral cephalometric radiographs. This protocol could position pediatric dental visits as an accessible touchpoint for early identification of children with unrecognized SDB and inform pathways for timely referral. Protocol Version: 1.4, dated 13 May 2026. Trial Registration: ClinicalTrials.gov NCT07581938.

## 1. Introduction

Sleep-disordered breathing (SDB) in children, including obstructive sleep apnea (OSA), produces recurrent intermittent hypoxia and sleep fragmentation that are associated with behavioral dysregulation, neurocognitive deficits, impaired growth, and adverse cardiometabolic outcomes [1,2]. The prevalence of OSA in children is estimated at 1–5%, while habitual snoring affects 10–27% of the pediatric population, making SDB one of the most common sleep disorders in childhood [3,4]. Craniofacial characteristics such as mandibular retrognathia, increased mandibular plane angle, and reduced nasopharyngeal airway dimensions have been associated with upper airway narrowing and increased SDB risk [5,6]. The consequences of delayed identification can be significant, including substantially elevated risk of anxiety (risk ratio [RR] 1.44), depressive disorders (RR 1.71), behavioral disorders (RR 1.31), and learning disorders (RR 1.39) at 1 year among children with delayed versus early surgical intervention [7]. Critically surgery within six months of diagnosis appreciably reduced the risk of these outcomes compared with delayed surgery, suggesting a time-sensitive window for intervention [7]. Despite these well-established associations, pediatric SDB remains under-recognized and under-diagnosed. The American Academy of Pediatrics recommends that all children be screened for snoring at every health maintenance visit [4]. Yet, systematic approaches to early risk identification outside of medical settings remain limited, even though a recent implementation study demonstrated that integrating a structured electronic sleep screener across primary care practices and well-child visits significantly increases sleep disorder diagnoses, polysomnography (PSG) orders, and referrals [8].

Pediatric dental providers routinely evaluate craniofacial growth and development, obtain lateral cephalometric radiographs, and assess clinical features such as high-arched palate, tonsillar hypertrophy, mouth breathing, and dental malocclusion—all of which have been associated with SDB risk and fall outside the typical assessment performed at a well-child visit [6,9,10,11]. Fagundes and Flores-Mir (2022) highlighted that specific craniofacial abnormalities frequently identified by dental professionals have been associated with pediatric OSA, and that dental professionals are well positioned to screen for these features because they assess children more frequently than physicians [11]. Additionally, pediatric dental providers have frequent longitudinal contact with children, providing additional touchpoints for screening that do not exist in the medical system and positioning them well to participate in early screening for SDB risk and to help narrow referrals for full medical assessment.

The Pediatric Sleep Questionnaire (PSQ) is a brief, parent-reported instrument that assesses snoring, breathing-related sleep disturbances, and daytime sleepiness. A cutoff score of ≥0.33 has been validated and widely applied in pediatric populations, including school-aged children, to identify those at increased risk for SDB [12,13,14,15,16]. While the PSQ is not intended as a diagnostic tool, this threshold is commonly used for screening and risk stratification to guide referral for further evaluation [17,18]. A growing body of international evidence supports the feasibility and clinical relevance of SDB screening in dental and orthodontic settings. Across eight studies enrolling 4610 children across 14 countries, PSQ-based screening has consistently identified 7–13% of children at risk for SDB, a rate 1.5 to 2.5 times higher than the approximately 5% prevalence reported in healthy general pediatric populations [19,20,21,22,23,24,25]. The convergence across diverse populations, clinical settings, and geographic regions suggests that dental and orthodontic clinics capture a clinically meaningful proportion of children with unrecognized SDB risk. A systematic review of 12 orthodontic-based studies totaling 3737 participants confirmed that SDB risk is consistently elevated in populations with malocclusions and craniofacial risk markers [26].

While PSG remains the gold standard for diagnosing pediatric OSA, significant barriers limit its use as a corroborative tool in screening-level research. PSG is resource-intensive, costly, and requires specialized equipment and trained personnel. There is a growing body of research documenting that in-laboratory PSG is associated with emotional distress, anxiety, and reduced cooperation in pediatric patients and that these factors can compromise test validity and completion [27,28,29,30,31]. Feasibility studies of home sleep testing in children have demonstrated good technical adequacy, with several reporting greater than 90% of recordings meeting predetermined quality criteria [32]. Advances in wearable sleep technology now complement questionnaire-based screening by enabling objective, home-based assessment of sleep and breathing patterns. FDA-cleared wearable devices can provide indicators of sleep efficiency, cardiopulmonary coupling, and estimated apnea burden across multiple nights, reducing both night-to-night variability and participant burden compared with laboratory-based polysomnography [16,32,33,34]. Wearable home-based sleep monitoring devices can provide physiologic markers of SDB risk without establishing a clinical diagnosis, making them well-suited for screening-level research. A 2026 scoping review of 34 studies on SDB screening in dental settings found that while the PSQ was the most commonly used screening tool, no study examined how screening protocols integrate within routine dental workflows, no study paired questionnaire-based screening with objective psychologic sleep measures, and only one study documented referral outcomes [35].

This prospective, cross-sectional observational study protocol aims to evaluate the feasibility and concordance of integrating questionnaire-based screening, wearable physiologic sleep data, and cephalometric craniofacial measurements in a comprehensive, dental-based approach to identifying children at increased risk for SDB. By combining the structural assessment expertise unique to dental providers with validated screening instruments and objective physiologic measures, this approach addresses gaps in the current screening landscape, complements the symptom = focused screening currently performed in primary care, and may facilitate more targeted referrals for definitive evaluation.

## 2. Materials and Methods

### 2.1. Study Design and Objectives

This is a prospective, cross-sectional observational study conducted at the University of North Carolina (UNC) Adams School of Dentistry (ASOD) Pediatric Dentistry Clinic. Children aged 8–13 years will be classified as low-risk or high-risk for SDB using the PSQ and will undergo anthropometric and airway assessments, validated psychosocial measures, and home sleep monitoring with an FDA-cleared wearable device, manufactured by SleepImage (MyCardio LLC, Denver, CO, USA).

The primary objective is to examine associations between PSQ-based SDB risk classification and objective physiologic sleep parameters obtained through home sleep monitoring. This study is designed as a screening concordance and feasibility investigation, not a diagnostic accuracy study; accordingly, PSG is not included as a reference standard, and findings should be interpreted as characterizing associations between screening-level risk classification and physiologic sleep parameters rather than as establishing diagnostic performance. Secondary objectives include evaluating associations between SDB risk classification and body mass index (BMI), Mallampati score, Brodsky tonsillar grade, and psychosocial functioning, specifically symptoms of anxiety, depression, perceived stress, and daytime sleepiness. An exploratory objective is to characterize craniofacial features associated with SDB risk among participants with clinically available lateral cephalometric radiographs. The inclusion of lateral cephalometric imaging when already clinically available does not exceed minimal risk, as radiation exposure is within the range of standard dental imaging routinely obtained in clinical care.

The planned sample size is 60 participants, with 30 participants classified into each risk group (low-risk vs. high-risk). This sample size is based on the primary aim of comparing physiologic sleep parameters derived from wearable home sleep monitoring between low- and high-risk groups. The minimum sample size per group was determined using the standard formula for comparing two independent group means:$$n=2{\left(\frac{Z_{1-\alpha /2}+Z_{1-\beta }}{d}\right)}^{2}$$
where $Z_{1-\alpha /2}$ = 1.96 (corresponding to a two-sided significance level of α = 0.05), $Z_{1-\beta }$ = 0.8416 (corresponding to 80% statistical power), and d = 0.80 (Cohen’s d, representing a large standardized effect size). Substituting these values yields$$n=2{\left(\frac{1.96+0.8416}{0.80}\right)}^{2}=2{\left(\frac{2.8016}{0.80}\right)}^{2}=2{\left(3.502\right)}^{2}=2\left(12.264\right)\approx 25\;\mathrm{per}\;\mathrm{group}$$

This yields a minimum of 25 participants per group. Enrollment was set at 30 per group (*N* = 60 total) to accommodate an anticipated attrition rate of approximately 20%, accounting for incomplete recordings, data quality exclusions, and participant withdrawal while preserving adequate statistical power for the primary analysis.

This study is powered to address the primary aim only. Secondary and exploratory analyses are intended to generate preliminary effect size estimates and variability data to inform future hypothesis-driven studies. Up to 300 individuals may be screened to achieve target enrollment, reflecting the expected distribution of risk classification within the clinic population and anticipated exclusions. A stratified quota sampling approach will be used to ensure balanced representation of each PSQ-defined risk group, a design feature that does not alter the cross-sectional nature of the study but ensures adequate statistical power for between-group comparisons. Participants who discontinue or have incomplete data will not be replaced.

The study was approved by the Institutional Review Board of the University of North Carolina (UNC) at Chapel Hill (IRB#25-3218, 26 January 2026) and registered at ClinicalTrials.gov (NCT07581938, 5 May 2026). Recruitment and follow-up procedures will be conducted between May 2026 and June 2027. This protocol is reported in accordance with the Standard Protocol Items: Recommendations for Interventional Trials (SPIRIT) 2025 statement [36] and adapted accordingly for this prospective, cross-sectional observational study. A completed SPIRIT 2025 checklist is provided as Supplementary Table S1.

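### The allowance for about 20% attrition is one participant per group short: 30 enrolled leaves 24 evaluable against the plan's own minimum of 25 (minor)

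*Protocol article*

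**What the plan says.** All of the relevant text is in section 2.1 of the protocol article.

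- **Inputs.** The formula for comparing two independent means is used with Z = 1.96 ("corresponding to a two-sided significance level of α = 0.05"), Z = 0.8416 ("corresponding to 80% statistical power") and d = 0.80 ("representing a large standardized effect size").
- **Result.** "This yields a minimum of 25 participants per group".
- **Enrolment.** "The planned sample size is 60 participants, with 30 participants classified into each risk group (low-risk vs. high-risk"). The step from 25 to 30 is made "to accommodate an anticipated attrition rate of approximately 20" per cent.
- **What the 20% covers.** It is described as "accounting for incomplete recordings, data quality exclusions, and participant withdrawal while preserving adequate statistical power for the primary analysis". It is therefore the whole loss from the primary analysis set, not withdrawal alone.
- **Replacement.** "Participants who discontinue or have incomplete data will not be replaced".

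Section 2.9 names independent-samples t-tests or Mann–Whitney U tests for the primary comparison. Section 2.5 requires at least two qualifying nights for inclusion in the primary analysis, which is one route by which enrolled children drop out of it.

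**The concern.** The minimum of 25 is a number of analysable participants, so the enrolment figure should leave 25 after the expected loss. Thirty is exactly 25 × 1.20. The text does not print that multiplication, but the figure matches it. Adding 20% to the target is not the same as allowing for a 20% loss from those enrolled, which requires dividing by 0.80. Because losses are not replaced, nothing later in the design makes up the difference.

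What is at stake is whether the protocol's only power statement agrees with itself. Section 2.1 says the study is powered for the primary aim alone, and the stated attrition takes the expected group size below the stated minimum.

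**Working it through.** **Inputs (section 2.1):** two-sided α = 0.05, power 80%, d = 0.80, equal groups, 30 enrolled per group, attrition about 20%, no replacement.

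**1. Reproduce the plan's minimum.**
n = 2 × ((1.96 + 0.8416)/0.80)² = 24.53, rounded up to 25 per group. This agrees with the protocol.

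**2. Apply the stated attrition to the stated enrolment.**
30 × (1 − 0.20) = 24 per group, 48 in total. This is below 25 and below 24.53, so rounding does not explain the gap.

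**3. Find the enrolment that fits the stated attrition.**
- From 25: 25/(1 − 0.20) = 31.25, so 32 per group (64 in total). Check: 32 × 0.80 = 25.6.
- From the unrounded 24.53: 24.53/0.80 = 30.66, so 31 per group.
- For comparison, 25 × (1 + 0.20) = 30, the figure in the protocol.

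**4. Find the attrition that 30 per group can absorb.**
- To keep 25: 1 − 25/30 = 16.7%.
- To keep 24.53: 1 − 24.53/30 = 18.2%.

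**5. Power at d = 0.80, two-sided α = 0.05.**
Normal formula: power = Φ(d × √(n/2) − 1.96). At n = 24 this is Φ(0.80 × √12 − 1.96) = Φ(0.811) = 79.1%.
t-test: noncentral t with 2n − 2 degrees of freedom and noncentrality d × √(n/2).

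| Evaluable per group | Plan's normal formula | t-test |
|---|---|---|
| 24 | 79.1% | 77.4% |
| 25 | 80.7% | 79.1% |
| 26 | 82.2% | 80.7% |

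**6. Separate the two sources of the t-test shortfall.**
Total below target: 80 − 77.4 = 2.6 points.
- Attrition, 25 falling to 24: 79.1 − 77.4 = 1.7 points.
- Normal approximation, already present at 25: 80 − 79.1 = 0.9 points.

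**7. Difference detectable with 80% power at 24 per group.**
- Normal formula: 2.8016 × √(2/24) = 0.81.
- t-test: 0.83.

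**8. Let the loss vary by chance.** Assume each child is lost independently with probability 0.20. A group of 30 then keeps 25 or more with probability 0.43, and both groups do so with probability 0.43² = 0.18. Average power is about 78.8% (normal) or 77.1% (t-test), close to the values at exactly 24.

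**The case against.** The strongest defence is that the protocol's wording is loose enough to cover the gap. It says approximately 20%, and it promises adequate power after attrition without repeating 80% at that point. Thirty per group is exact at 16.7% attrition, the shortfall is one child per group, and by the plan's own formula power drops only to 79.1%. In a study described as a concordance and feasibility investigation, with effect sizes reported, a difference of one to three points would not change how a null result is read.

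This defence settles the grade: the matter is minor. It does not remove the inconsistency. Section 2.1 calls 25 a minimum, gives 80% as its only power figure, and states an attrition rate under which the expected number is 24. If 16.7% was the working assumption, the text should say so.

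It is also fair to object that 77.4% should not be charged to attrition alone. The normal-approximation formula is stated openly and its result reproduces. Using the t distribution is a refinement, and 25 per group gives only 79.1% by that method before any loss. That part of the objection stands in full, and the two contributions are shown separately above.

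**Conclusion.** The attrition allowance is wrong as written, and the consequence is small. Under the stated 20% loss without replacement, 24 per group are evaluable against a stated minimum of 25. Power for d = 0.80 is then 79.1% by the plan's formula (80% power for d = 0.81) or 77.4% by t-test (80% power for d = 0.83). These figures assume equal loss in the two groups and take d = 0.80 and the 20% as given.

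A reader might infer three stronger things that the document does not support:

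- **That the study is seriously underpowered or the primary analysis compromised.** The gap is one participant per group, and no endpoint or analysis changes.
- **That attrition alone costs 2.6 points, or that the plan's own minimum implies 33 per group.** The 2.6 points combine two causes. Thirty-three comes from replacing 25 with the t-test figure of 26 (26/0.80 = 32.5). The plan's own minimum gives 32.
- **That a Mann–Whitney test would lower power further by a known amount.** The usual efficiency figure assumes normal data. Section 2.9 offers that test where appropriate, which would mainly be where normality is in doubt, so no such figure can be attached.

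**What to change.** Either of two edits to section 2.1 is enough, and neither adds participants:

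1. Keep 30 per group and 20%, and state the result: with 30 enrolled per group and 20% attrition, 24 per group are evaluable, giving about 79% power by the stated formula (about 77% by two-sample t-test) for d = 0.80. Name the method beside each figure, so that the lower value is not read as the effect of attrition alone.
2. Keep 30 and 25, and state that the enrolment allows for about 16.7% attrition.

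The cost is a sentence or two and, under the first option, a slightly less favourable power figure. If the sponsor prefers to keep 20% attrition together with the minimum of 25, the consistent enrolment is 25/0.80, rounded up to 32 per group. That is 64 in total, four more than planned.

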### 2.2. Study Setting and Recruitment Workflow

Participants will be recruited from the Pediatric Dentistry Clinic at the UNC ASOD, a university-based practice providing comprehensive oral healthcare for children and adolescents. Recruitment will occur among patients presenting for new patient examinations, periodic recall visits, and other routine dental appointments.

Research personnel will review upcoming clinic schedules and electronic health records under an Institutional Review Board (IRB)-approved limited Health Insurance Portability and Accountability Act (HIPAA) waiver to identify children within the eligible age range and assess preliminary eligibility. Parents or legal guardians of potentially eligible participants may be contacted by telephone prior to the scheduled dental appointment to introduce the study and assess interest. Families who cannot be reached by telephone or who prefer to discuss participation in person may be approached at the time of their child’s scheduled visit. Following confirmation of eligibility and informed consent and assent completion by trained study personnel, participants will complete baseline study assessments either immediately before or after their dental appointment to minimize additional visits.

### 2.3. Screening and Eligibility

Children meeting all inclusion criteria and none of the exclusion criteria will be eligible for enrollment. The age range of 8–13 years was selected to capture a developmental period when SDB may influence craniofacial growth and psychosocial functioning while also allowing reliable completion of self-report measures.

Eligible participants will be children aged 8–13 years receiving care at the UNC ASOD Pediatric Dentistry Clinic with an American Society of Anesthesiologists (ASA) Physical Status Classification of I or II. Participants must be able to read and understand English or Spanish, provide assent with parental or guardian consent, and have access to a smartphone compatible with the home sleep monitoring application.

Participants will be excluded if they have a prior diagnosis of SDB or OSA, history of adenotonsillectomy, craniofacial syndromes or conditions known to substantially alter craniofacial morphology, prior or current orthodontic treatment, or prior orthognathic surgery. These exclusion criteria were selected to reduce heterogeneity in upper airway anatomy and SDB risk factors that could confound interpretation of physiologic sleep and craniofacial outcomes.

### 2.4. PSQ-Based Risk Classification

SDB risk will be assessed using the PSQ, a validated caregiver-completed screening instrument widely used in pediatric research and clinical settings [12]. PSQ scores will be calculated by dividing the number of affirmative responses by the total number of completed items. Participants will be classified as low-risk (PSQ score < 0.33) or high-risk (PSQ score ≥ 0.33) based on the established threshold for pediatric SDB risk stratification. Detailed administration procedures, scoring algorithms, handling of missing data, interpretation thresholds, and psychometric properties for the PSQ are provided as Supplementary Materials [12,37,38,39,40,41,42,43].

The PSQ is used in this study to stratify participants by SDB risk rather than to establish a clinical diagnosis. No diagnostic determinations will be made based on questionnaire responses alone.

### 2.5. Home Sleep Monitoring Methods

Objective physiologic sleep data will be collected using the SleepImage Ring, an FDA-cleared wearable home sleep monitoring device, and analyzed using the FDA-cleared SleepImage System (Version 2.28, MyCardio LLC, Denver, CO, USA). Following completion of baseline assessments, participants will receive the device along with standardized instructions for use, charging, and smartphone application synchronization. Participants and their parents or guardians will be instructed to maintain usual sleep routines throughout the monitoring period.

Participants will wear the device during sleep for a minimum of three consecutive nights. To accommodate scheduling challenges, missed nights, and device return logistics, participants will be permitted up to three weeks to complete the required monitoring period. Physiologic sleep data will be collected passively during sleep and transmitted through a secure, HIPAA-compliant platform.

Primary physiologic sleep outcomes will include the cardiopulmonary coupling (CPC) software-derived Apnea-Hypopnea Index (sAHI), software-derived Respiratory Disturbance Index (sRDI), Sleep Apnea Indicator (SAI), and Sleep Quality Index (SQI), provided as continuous data. To ensure adequate data quality, only recordings with an average signal quality of at least 50% and a minimum sleep duration of four hours per night will be included in analyses. A minimum of two qualifying recording nights will be required for a participant’s data to be included in the primary analysis. Participants with only one qualifying night will be excluded from the primary analysis but will be retained for sensitivity analyses.

Adherence will be supported through brief telephone check-ins approximately one and two weeks following device distribution to address technical questions and encourage compliance. Home-based monitoring was selected over laboratory polysomnography to enable assessment within the participant’s natural sleep environment while minimizing burden and supporting feasibility within a pediatric dental setting.

